### Cardiovascular assessment

#### Cardiovascular assessment by the pulse wave analysis

Pulse wave analysis will be performed using SphygmoCor equipment (SphygmoCor, AtCor Medical, Sydney, Australia). In a supine position, the patient will have a pneumatic clamp placed in the proximal portion of the left arm. Following that, additional data such as age, weight, and height will be provided to the system. After a 10-min rest, three measurements of systolic and diastolic arterial pressure will be performed in a 2-min interval [61] and accepted as long as the difference is less than 10% [62], or 5 mmHg [63] between the measurements. Afterward, the mean value of the three accepted measurements will be inserted into the system to obtain the MAP, SBPc, SBPp, DBPc, and DBPp [64–67]. In T0, the variables will be measured after 10 min of rest. In T1, it will be taken prior (10 min), during (23 and 37 min), and after (47 min) the training session. The average between minutes 23 and 37 (pause between sets) will be used as the exercise value.

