Abe et al. [39] highlighted the intensity of exercise associated with BFR as an important aspect to optimize neuromuscular adaptations. Thus, Gorgey et al. [40] demonstrated a 17% increase in muscle mass after BFR combined with electrical stimulation in spinal cord-injured patients, compared to isolated electrical stimulation. Given the impossibility of performing active exercises, it seems also necessary to investigate the effects of BFR associated with PM and combined with electrical stimulation (BFRpE) in comatose patients to prevent muscle atrophy and weakness and possibly to optimize physical function and quality of life in ICU survivors.

Regarding BFR safety, after the release of between-sets BFR, rapid local muscular blood inflow and bulky venous return occur [41], which can lead to unknown repercussions in the cardiovascular system [42]. Consequently, these repercussions may reflect in critical changes in vital signs of severely ill patients and therefore in health recovery.

Hence, the present study aimed to investigate the effect of BFRp and BFRpE on cardiovascular safety and applicability, neuromuscular adaptations, physical function, and quality of life in ICU coma patients. We hypothesized that there will be no negative cardiovascular repercussions of BFRp, BFRpE, and BFRp will be able to reduce and BFRpE to prevent muscle atrophy and weakness, in addition to exerting more positive effects on physical function and on quality of life compared to BFRp.

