#### Primary outcome measurements

##### Acute cardiovascular responses

The first training session (T1) will immediately succeed T0 and will have the monitoring of acute cardiovascular responses to training. Mean arterial pressure (MAP), central and peripheral systolic blood pressure (SBP [SBPc and SBPp]), and central and peripheral diastolic blood pressure (DBP [DBPc and DBPp]) will be measured by pulse wave analysis. Concomitantly, the heart rate (HR) and peripheral oxygen saturation (SpO_2_) should be recorded through a portable vital signal monitor (Dixtal, DX 2021, Amazonas, Brazil) every 2 min. The mean of 5 recordings at rest (10 min of rest), 18 recordings during exercise (~ 37 min of training), and the average of 5 post-exercise recordings (10 min) will be considered in the analysis. Electrocardiographic signals will be monitored, and, in case of adverse events, the session will be promptly interrupted. The training protocol will be applied to both legs during the session, simultaneously and alternately between the stimulated leg and the rest of the contralateral limb [37].

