##### Passive mobilization/control group protocol (PM)

The PM protocol will be modified from Barbalho et al. [37]. The authors applied 3 sets of 15 mobilizations for flexion and extension of the hips, knees, and ankles. Movement was standardized in 2:2 using a metronome (2 s flexion and 2 extension), totaling 3 min of PM. To standardize PM with the BFR protocol, in every minute of PM, 1 min of rest will be allowed, totaling 5 min of PM for each set. Following that, a 3-min rest will be allowed, and the mobilization will be repeated in 5 sets. The session will last 37 min on average [56].

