##### Passive mobilization associated with blood flow restriction protocol (BFRp)

A pressure cuff with 17.5 cm of width and 94 cm of length (JPJ, Sao Paulo, Brazil) with a pressure manometer will be placed on the quadriceps muscle, on the inguinal fold. Afterward, a vascular Doppler probe (DV-600; Martec, Ribeirao Preto, Brazil) will be placed in the posterior tibial artery. To determine the occlusion pressure, the cuff will be inflated until the auscultatory pulse stops [57]. An external compression of 85% of the total vascular occlusion pressure will be applied for 5 min, followed by a 3-min rest (compression release) [42]. The BFR protocol will be synchronized to the PM protocol. Compression will be repeated 5 times during the training session, and occlusion pressure will be re-evaluated in all sessions.

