##### Passive mobilization associated with blood flow restriction and combined with neuromuscular electrical stimulation (BFRpE)

The procedures for BFRp will be adopted and synchronized with an electrical stimulation protocol. For the electrical stimulation electrode placement, the skin will be subjected to trichotomy, abrasion, and asepsis. Rectangular-shaped electrodes (50 × 50 mm) will be placed on the distal and proximal motor points of the VL (proximal and distal points located between the reference line of the antero-superior iliac spine and the superior lateral border of the patella and on the line between the apex of the great trochanter and the superior lateral border of the patella, respectively), RF (located on the reference line between the antero-superior iliac spine and the superior patella border), and AT (on the line between the apex of fibular head and the medial malleolus). In addition to the reference lines, the placement of the electrodes demonstrated in Santos et al. [58] and Dirks et al. [59] will be used to guide the location and electrostimulation of VL, RF, and TA. Additionally, this electrode placement will be marked with a semi-permanent pen to maintain the stimulus points throughout the study. A biphasic electro stimulator (Dualpex 071, Quark Medical, Piracicaba, Brazil) will provide symmetric pulses of 100 Hz, pulses lasting 400 μs, 5 s on (0.75 s rise, 3.5 s contraction and 0.75 s decay), and 10 s off, the intensity must be capable of causing visible contractions. The mean intensities used should be maintained from 29 to 33 mA and increased in approximately 3 min, when muscle contraction is no longer visible. The session will last 40 min, including 30 min of stimulation, a 5-min warm-up, and a 5-min cool-down, both with 5 Hz of frequency, pulse wave lasting 250 μs, and sub-maximal intensities (without muscle contraction) [59, 60]. The same researcher will apply both the BFRp and electrical stimulation.

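### The T1 blood-pressure exercise value averages minutes 23 and 37 as if both were between-set pauses, which the protocol's own schedule contradicts; it is not tied to cuff release

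*Protocol article*

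**What the plan says.** All references are to the protocol article.

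- **Cardiovascular assessment by the pulse wave analysis** sets the T1 times: "In T1, it will be taken prior (10 min), during (23 and 37 min), and after (47 min) the training session". It then reduces the two during-session readings to one number: "The average between minutes 23 and 37 (pause between sets) will be used as the exercise value". For the readings behind each value it says that "three measurements of systolic and diastolic arterial pressure will be performed in a 2-min interval", accepted if they differ by less than 10% or 5 mmHg.
- **Passive mobilization/control group protocol (PM)** gives 5-min sets, after which "a 3-min rest will be allowed, and the mobilization will be repeated in 5 sets", with a session of 37 min on average.
- **The BFRp section** says that the compression "will be applied for 5 min, followed by a 3-min rest (compression release"), five times per session and synchronized to the PM schedule.
- **The BFRpE section** adopts the BFRp procedures but gives another length: "The session will last 40 min, including 30 min of stimulation, a 5-min warm-up, and a 5-min cool-down".
- **Acute cardiovascular responses** has HR and SpO2 recorded every 2 min and analyses the mean of "18 recordings during exercise (~ 37 min of training"), with separate means of five recordings at rest and five after exercise.
- **Background** gives the safety rationale: "after the release of between-sets BFR, rapid local muscular blood inflow and bulky venous return occur", with unknown cardiovascular repercussions.

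**The concern.** Cardiovascular safety is a primary objective, and the hazard that the article names is an event: the inflow and venous return when the cuff is released between sets. The BP exercise value should therefore be read at a known point relative to a release, and at the same point in each arm. Instead it is fixed by clock minutes that do not match the phase claimed for them, and two readings from different phases are averaged. For HR and SpO2, the mean over the whole training period pools post-release recordings with all the others.

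At stake is how far the acute-response summaries can speak to the release response. These responses are measured only at the first training session, so a badly timed BP reading cannot be replaced later.

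**Working it through.** **1. The plan's own figures.** Inputs: 5 sets of 5 min and 3-min rests (PM and BFRp sections). Session length = 5 × 5 + 4 × 3 = 25 + 12 = 37 min, as stated. One recording every 2 min gives 37 / 2 = 18.5, so 18 whole recordings, as stated. The set-and-rest schedule is thus reproduced exactly.

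**2. Where minutes 23 and 37 fall.** The article does not say what minute 0 is. From the start of training, the sets run 0-5, 8-13, 16-21, 24-29 and 32-37, and the between-set pauses are 5-8, 13-16, 21-24 and 29-32. From the start of the 10-min rest, add 10 to each.

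| Minute 0 | Minute 23 | Minute 37 | Minute 47 |
|---|---|---|---|
| Start of training | pause, 2 min after third release | end of set 5 and of training | 10 min after training |
| Start of 10-min rest | end of set 2 | 3 min into set 4, under compression | end of training |
| Start of a 5-min stimulation warm-up (assumed for BFRpE, compression starting after it) | 2 min into set 3 | start of set 5 | 5 min after training |

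On none of these clocks are both minutes in a between-set pause. Minute 47 does not settle the choice: it equals 37 + 10 (training plus post-exercise period) and also 10 + 37 (rest plus training).

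**3. A check that does not depend on the clock.** One cycle is 5 + 3 = 8 min. The readings are 37 − 23 = 14 min apart, and 14 = 8 + 6. Minute 37 therefore always sits 6 min later in the cycle than minute 23 (equivalently, 2 min earlier), and the two can never be at the same delay after release. Both could lie inside a between-set pause only if training began between minutes 7 and 8, or between 15 and 16. Even then the delays would be 2-3 min and 0-1 min, and the article names no event at those times. A response present at only one of the two minutes is halved in their average.

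**4. Three readings per value.** If the readings are 2 min apart they span 2 × 2 = 4 min, longer than a 3-min pause. If the wording means three readings within 2 min, they fit. The text allows both.

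**5. Session lengths.** 30 + 5 + 5 = 40 min for BFRpE against 37 min for PM. If compression starts with the stimulation warm-up, minute 37 falls in the cool-down (35-40). If it starts after the warm-up, the last compression ends at 5 + 37 = 42 min, beyond the stated 40. The article does not say which.

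**6. The 18-recording mean.** Clock from the start of training, between-set releases at 5, 13, 21 and 29 min. The article gives no surge duration; 2 to 3 min is an assumption.

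- 2-min surge: recordings at even minutes catch it at 6, 14, 22 and 30; at odd minutes at 7, 15, 23 and 31. Either way 4/18 = 22%.
- 3-min surge: even minutes catch it at 6, 8, 14, 16, 22, 24, 30 and 32, so 8/18 = 44%. Odd minutes catch 4/18 = 22%.
- A 1-min surge would be caught by 4 of 18 or by none, depending on the grid.

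**The case against.** The best reply is that only the label is certainly wrong. On the start-of-training clock minute 23 follows a release by 2 min and minute 37 coincides with the fifth release, so both readings may be made with the cuff down. The five post-exercise HR and SpO2 recordings also begin straight after that release. This stands in part: a reader might infer that the exercise value is certain to miss the surge, and the article does not support that. It also does not fix this clock, and even on it the two delays after release differ.

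Other stronger inferences fail too:

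- That the BP value is averaged over the session. It averages two time points; the 18-recording mean is a separate rule for HR and SpO2.
- That the agreement rule screens out a transient at T1. The rule is introduced for readings after a 10-min rest and is not expressly extended to exercise.
- That BFRpE is read in a different cuff phase from BFRp. This depends on where the stimulation warm-up sits relative to the first compression, which the article leaves open.
- That a surge of some stated size would be needed to reach the 20%-of-baseline limit. The article does not say that this limit applies to the averaged values.

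Both legs are trained simultaneously and alternately, so a single set-and-rest clock may not describe both cuffs. That limits certainty about cuff state at any minute, but it also adds to the case for stating the clock.

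Finally, ECG monitoring and absolute limits for HR, BP, MAP and SpO2 operate independently of the averages, so a large excursion can still stop a session. This is a real safeguard, although ECG does not measure pressure and the article describes no other scheduled BP reading during exercise.

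**Conclusion.** The point holds in a limited form. The description of minutes 23 and 37 contradicts the article's own 37-min schedule on both natural clocks. The BP exercise value mixes phases and is not anchored to between-set release. A transient response may be diluted (halved, if present at only one of the two minutes) or caught only by chance. That conclusion rests on the stated set and rest lengths and on a single cycle for the session.

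For HR and SpO2, 22-44% of the averaged recordings would carry a post-release response, on the assumption that it lasts 2 to 3 min after each of the four between-set releases. A longer or shorter response changes that range. The finding concerns how well the acute-response summaries answer the safety question; it does not show that harm would go unnoticed at the bedside.

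**What to change.** 1. Reconcile the acute-response section, the three intervention sections and the pulse-wave section on one clock. State minute 0, what each leg's cuff is doing, and how the 37-min and 40-min sessions and the stimulation warm-up and cool-down line up.
2. Define the T1 exercise BP readings by event: the same named between-set releases in all three arms, with the matching pause in PM.
3. State whether the three-reading agreement rule applies only to resting values, and how the three readings are spaced.
4. Report each patient's maximum and minimum HR and minimum SpO2 during exercise beside the 18-recording mean.

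Items 1 and 3 are wording, and item 4 uses recordings already made. Item 2 has a real cost: Trial status reports that recruitment opened, and a first participant was enrolled, in April 2020, so it changes how a primary outcome is measured part-way through. Patients measured under the old timing should be identified in the analysis.

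### The primary exercise pressure is defined as the average of two between-set pause readings, but minute 37 lies in no between-set pause on either clock built from the protocol's own durations

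*Protocol article*

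**What the plan says.** Pulse-wave pressures (mean arterial, and central and peripheral systolic and diastolic) at the first training session, T1, are listed among the primary outcome measurements. The section on pulse wave analysis gives their times: "In T1, it will be taken prior (10 min), during (23 and 37 min), and after (47 min) the training session". It then defines the in-session value: "The average between minutes 23 and 37 (pause between sets) will be used as the exercise value".

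The session is laid out in the intervention sections. On the length of one set: "in every minute of PM, 1 min of rest will be allowed, totaling 5 min of PM for each set". On the sequence: "Following that, a 3-min rest will be allowed, and the mobilization will be repeated in 5 sets". On the total: "The session will last 37 min on average". In the BFRp arm the cuff is compressed for 5 min and released for 3 min, five times, and "The BFR protocol will be synchronized to the PM protocol".

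The Background names the moment of interest for safety: "after the release of between-sets BFR, rapid local muscular blood inflow and bulky venous return occur".

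**The concern.** The protocol treats both in-session readings as taken in a pause between sets, which would make them like with like and justify averaging them. Its own session layout does not put minute 37 in such a pause, and minute zero is never defined.

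This matters because cardiovascular safety is a primary objective and this average is the only in-session pressure value that the protocol defines. The hazard it names is cuff release. If one reading follows a release and the other does not, or the two follow at different delays, their mean has no clear physiological meaning, and a response confined to one of them is diluted. If the clock also runs differently in different arms, the between-group comparison at T1 compares different phases.

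**Working it through.** **Inputs.** Set length 5 min, rest 3 min and 5 sets (PM protocol). Cuff compressed 5 min and released 3 min, five times, in step with the sets (BFRp protocol). Readings at 10, 23, 37 and 47 min (pulse wave analysis). Rest of 10 min, training of about 37 min, post-exercise period of 10 min (Acute cardiovascular responses).

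**Step 1: reproduce the session length.** 5 × 5 + 4 × 3 = 25 + 12 = 37 min, as stated. The layout is therefore five sets with four pauses between them.

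**Step 2: build the grid.** If training starts at clock minute s, set i runs from s + 8(i − 1) to s + 8(i − 1) + 5. Its end is a cuff release, and a 3-min pause follows sets 1 to 4. Two starts follow from the stated durations: s = 0 (clock starts with set 1) and s = 10 (clock starts with the rest period).

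| | s = 0 | s = 10 |
|---|---|---|
| Sets | 0–5, 8–13, 16–21, 24–29, 32–37 | 10–15, 18–23, 26–31, 34–39, 42–47 |
| Pauses | 5–8, 13–16, 21–24, 29–32 | 15–18, 23–26, 31–34, 39–42 |
| Releases | 5, 13, 21, 29, 37 | 15, 23, 31, 39, 47 |
| Minute 23 | 2 min into pause 3 | end of set 2, first instant of pause 2 |
| Minute 37 | end of set 5; no set follows | 3 min into set 4, cuff inflated |
| Minute 47 | 10 min after training | end of training; no recovery value |

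The text does not choose between them. Read as a clock time, the prior reading at 10 fits s = 10. A recovery reading at 47 fits s = 0, since 37 + 10 = 47; but 10 + 37 = 47 as well.

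**Step 3: other starts.** Both 23 and 37 fall in a pause only for s of about 7–8 or 15–16. Nothing in the text gives a start at 7–8. With s = 15–16, training ends at 52–53, so 47 could not be after the session.

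**Step 4: releases with a pressure reading before the next inflation.** For s = 0, the releases at 5, 13 and 29 have none. For s = 10, the releases at 15, 31 and 39 have none. That is 3 of 5 on either clock, counting a reading that coincides with a release as taken after it.

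**Step 5: effect of averaging.** With changes d1 and d2 at the two readings, the exercise value shows (d1 + d2)/2. If d2 = 0 this is d1/2. For an assumed d1 = −20%, the average is −20% if d2 = −20%, −10% if d2 = 0, −5% if d2 = +10%, and 0 if d2 = +20%. The protocol gives no figure for d1 or d2, so these values only show the range.

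**Step 6: the BFRpE arm.** Its session is stated as 40 min, with a 5-min warm-up and a 5-min cool-down. If its clock starts at the warm-up (s = 5), the sets are 5–10, 13–18, 21–26, 29–34 and 37–42. Minute 23 is then 2 min into set 3, and minute 37 is the end of pause 4. The two readings are still unlike, and they no longer match the other arms.

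**Step 7: time needed per reading.** The same section describes three measurements at 2-min intervals, which span 2 × 2 = 4 min. If that applies in-session, it does not fit a 3-min pause.

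**The case against.** The strongest reply is that the session clock (s = 0) fits better, because it leaves a recovery value 10 min after training. On that clock minute 37 is also the instant of the fifth release, so a reading taken just afterwards is in the released state, as at minute 23. This stands in part. It means that opposite cuff states are not established; mid-compression at minute 37 arises only on the rest-inclusive clock. It does not rescue the definition: no set follows minute 37, and the two readings still differ in time since release.

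Second, training alternates between the legs, and the protocol does not say how the five compressions are shared between limbs. The grid assumes a single sequence, which is the one that reproduces 37 min. This is a real assumption, and it is a further reason to state the cuff state for each reading.

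Third, a reader might infer that the averaging blunts the 20% limit, so that a one-phase change would have to exceed 40% to count, and that a BFR arm could then pass as safe. The section on cardiovascular safety and applicability does not say that its 20% limit is applied to this average. Nor are its interruption criteria, or its rules on unsafe patients, adverse events and venous thrombosis, stated to use it.

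Fourth, a reader might infer that most releases go unmonitored. Heart rate and oxygen saturation are recorded every 2 min, so every 3-min pause contains at least one recording, and the ECG is monitored. What is sparse is pulse-wave pressure.

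**Conclusion.** The point holds as an error in the definition of a primary measurement. On both clocks that the stated durations support, minute 37 is not in a pause between sets. The exercise value therefore averages readings at different times since release (s = 0), or one at the onset of release and one under compression (s = 10). A change present at only one reading is halved, and 3 of 5 releases have no pulse-wave pressure reading before the next inflation. On the rest-inclusive clock there is also no recovery pressure.

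This rests on one sequence of five sets with the cuff in step, and on minute zero being the start of either set 1 or the rest period. The documents do not support naming a particular release as certainly covered: the third is covered for s = 0, but not for s = 10. They also do not show which way pressure moves in each phase, so the actual bias cannot be sized, and a wrong safety conclusion is not demonstrated.

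**What to change.** - Define minute zero for T1 measurements.
- For each pressure reading, state the set, the cuff state and the time since release (in the PM arm, the matching point of the set schedule), the same in all three arms. This requires reconciling the 40-min BFRpE session and its warm-up with the 37-min session, and saying how compressions are shared between the legs.
- Place both in-session readings at the same point of a between-set pause, and correct the label so that it describes them.
- Say whether the three measurements at 2-min intervals apply in-session. If they do, the timing must be reworked, because 4 min does not fit a 3-min pause.
- Keep the two readings as separate time levels in the T1 mixed model instead of averaging them.
- Reconcile the sections on acute responses, safety and applicability, the three interventions and pulse wave analysis, and state which value the 20% limit uses. Applying the limit to the larger of the two changes would alter a safety rule, not clarify it, so it should not be brought in as part of this repair.

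The cost is protocol wording and one more time level in the T1 model.
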